# Assessing the efficacy, safety and utility of hybrid closed-loop glucose control compared with standard insulin therapy combined with continuous glucose monitoring in young people (≥16 years) and adults with cystic fibrosis-related diabetes (CL4P-CF study): protocol for an open-label, multicentre, randomised, two-arm and single-period parallel trial

**DOI:** 10.1136/bmjopen-2025-111408

**Published:** 2025-10-29

**Keywords:** Cystic fibrosis, General diabetes, Quality of Life

## Abstract

**Introduction:**

Cystic fibrosis-related diabetes (CFRD) is one of the most clinically impactful comorbidities associated with cystic fibrosis (CF). Current recommended management with insulin therapy is challenging due to variable daily insulin requirements and adds to the significant burden of self-management. This study aims to determine if hybrid closed-loop insulin delivery can improve glucose outcomes compared with standard insulin therapy with continuous glucose monitoring (CGM) in young people (≥16 years) and adults with CFRD.

**Methods and analysis:**

This open-label, multicentre, randomised, two-arm, single-period parallel design study aims to randomise 114 young people (≥16 years) and adults with CFRD. Following a 2–3 weeks’ run-in period, during which time participants use a masked CGM, participants with time in target glucose range (3.9–10.0 mmol/L) <80% will be randomised to 26 weeks with hybrid closed-loop insulin delivery or standard insulin therapy with CGM. The primary outcome is the between-group difference in time in target glucose range (3.9–10.0 mmol/L) based on CGM levels during the 26-week study phase. Analyses will be conducted on an intention-to-treat basis. Key secondary outcomes are time above target glucose range (>10.0 mmol/L), mean glucose and HbA1c. Other secondary efficacy outcomes include glucose and insulin metrics, change in forced expiratory volume in 1 s and body mass index. Safety, utility, participant experiences and participant-reported outcome measures will also be evaluated. The trial is funded by the National Institute for Health and Care Research.

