## Methods and analysis

### Overview

The study adopts an open-label, multicentre, randomised, two-arm, single-period parallel design to assess the effect of HCL insulin delivery with CGM in young people (≥16 years) and adults with CFRD over 26 weeks compared with standard insulin therapy with CGM over 26 weeks (figure 1). Participants include young people aged 16 years and over and adults with CFRD requiring insulin therapy. The study aims for 114 participants completing the study. Recruitment will target up to 128 participants to allow for withdrawals. After a run-in period, eligible participants will be randomly assigned to 26 weeks of study intervention.

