### Sample size calculation

The primary analysis will evaluate the between-group difference in the proportion of time in target glucose range of 3.9 and 10.0 mmol/L based on sensor glucose from initiation of the treatment arm to 26 weeks. Data from four studies were considered when preparing the sample size calculations for this study.^18^,^21^ For a clinically important 5.0 percentage point absolute mean difference in time with glucose in target range,^22^ an SD of 8.1, 90% power, two-sided t-test at 5% significance level and 1:1 randomisation, total sample size is estimated to be 114 participants (57 per treatment group). Allowing for 10% loss to follow-up (5–8% in previous studies), we aim to randomise a total of 128 participants (64 per treatment group).

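### The abstract gives 114, the number needed with outcome data, as the number to randomise; the sample-size section aims to randomise 128

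*Protocol article*

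**What the plan says.** Three places in the protocol article give the trial's size.

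- **Abstract, Methods and analysis:** the study "aims to randomise 114 young people (≥16 years) and adults with CFRD".
- **Methods and analysis, Overview:** "The study aims for 114 participants completing the study", followed by "Recruitment will target up to 128 participants to allow for withdrawals".
- **Sample size calculation:** the inputs are a difference of 5.0 percentage points in time in range and "an SD of 8.1, 90% power, two-sided t-test at 5% significance level and 1:1 randomisation". From these, "total sample size is estimated to be 114 participants (57 per treatment group"). The section then continues: "Allowing for 10% loss to follow-up (5–8% in previous studies"), "we aim to randomise a total of 128 participants (64 per treatment group").

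**The concern.** The abstract and the sample-size section both state an aim, and both use the verb randomise, yet one gives 114 and the other 128. They cannot both be right. In the sample-size section 114 is the figure before the allowance for loss, and in the Overview it is the number who finish. The abstract has attached that figure to the wrong stage of the trial.

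Two things are at stake. First, the 90% power claim rests on about 114 participants with outcome data. Randomising 114 would meet it only if nobody were lost. Second, readers will later compare the number achieved with the number planned. With both figures in print as randomisation targets, a final count between 114 and 128 could be described either as on target or as short.

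**Working it through.** **Inputs** (all from Sample size calculation): difference δ = 5.0 percentage points; SD σ = 8.1; two-sided α = 0.05; power 90%; 1:1 allocation; loss 10%, with 5–8% in previous studies.

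**Step 1: reproduce the plan's 114.** For a two-sample t-test with n per group, power comes from the noncentral t distribution with 2n − 2 degrees of freedom and noncentrality δ / (σ√(2/n)).

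- n = 56: power 89.9%.
- n = 57: noncentrality 5.0 / (8.1 × √(2/57)) = 5.0 / 1.517 = 3.30; power 90.4%.

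The smallest n reaching 90% is 57 per group, so 114 in total. This matches the plan. The normal approximation gives 2 × (8.1 × (1.960 + 1.282) / 5.0)² = 55.2, so 56 per group. The plan's figure is therefore the t-test result, as it says.

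**Step 2: reproduce the plan's 128.** 57 / (1 − 0.10) = 63.3, rounded up to 64 per group, so 128 in total. This also matches. The allowance is slightly generous: 128 can lose 14 participants (14/128 = 10.9%) and still leave 114.

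**Step 3: power under each randomisation target.** The number with data is N × (1 − loss), split equally, and those lost are assumed to contribute no primary-outcome data.

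| Randomised | Loss | With data | Per group | Power |
|---|---|---|---|---|
| 128 | 10% | 128 × 0.90 = 115.2 | 57.6 | 90.7% |
| 114 | 0% | 114 | 57 | 90.4% |
| 114 | 5% | 114 × 0.95 = 108.3 | 54.15 | 88.9% |
| 114 | 8% | 114 × 0.92 = 104.9 | 52.44 | 87.9% |
| 114 | 10% | 114 × 0.90 = 102.6 | 51.3 | 87.2% |

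Against the stated 90%, randomising 114 falls short by 90 − 88.9 = 1.1 points at 5% loss, 90 − 87.9 = 2.1 points at 8%, and 90 − 87.2 = 2.8 points at 10%.

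**Step 4: which figure is out of place.** The sample-size section has 114 needed and 128 randomised. The Overview has 114 finishing and up to 128 recruited to cover withdrawals. These use the two numbers in the same way. Only the abstract ties 114 to randomisation.

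**The case against.** The strongest reply is that this is a slip in an abstract. The dedicated section states the target explicitly, its arithmetic is correct, and nothing in the article says that enrolment closes at the abstract's number. That stands, and it limits the severity. It does not remove the contradiction, because giving the wrong figure goes beyond condensing the text.

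A second reply is that the Statistical analysis section keeps dropouts and withdrawals in the intention-to-treat analysis. The primary outcome also accumulates from CGM over 26 weeks, so someone who leaves early may still contribute. If all 114 supplied data, power would be 90.4%. This also stands in part: the figures in the working assume the opposite. However, the plan itself allows for 10% loss, and including a participant in the analysis set does not create glucose data that were never recorded.

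A reader might go further and infer three incompatible targets, taking the Overview's 128 as a cap on people consented before the run-in. Those who fail the run-in would then reduce the number randomised below 128. The article does not support this. It does not define recruitment as consent, and the Overview's figures agree with the sample-size section on their natural reading. It gives no run-in failure rate from which a loss of power could be worked out. The word is ambiguous, because consent and run-in come before randomisation and some withdrawals are planned at that stage, but an ambiguity is not a third target.

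Nor does it follow that only the sample-size section preserves 90% power. The Overview's aim of 114 finishing gives 90.4%.

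**Conclusion.** The point holds as one direct contradiction, with an ambiguous word in the Overview beside it. The abstract states the completer number as the randomisation target, while the sample-size section aims to randomise 128. The sample-size calculation is sound and needs no change.

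The consequence is modest. If the abstract's figure were followed, power would be about 87% at the plan's own 10% loss and 88–89% at the 8–5% loss of previous studies. This rests on the plan's difference, SD and t-test, on equal loss in the two groups, and on lost participants giving no primary-outcome data. Any partial data from them would narrow the gap.

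Severity is minor: a reporting error in a core design figure, with no evidence that the trial is being run to the wrong target.

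**What to change.** 1. In the abstract, state that the study aims to randomise 128 participants (64 per group) so that 114 (57 per group) complete.
2. In the Overview, replace the recruitment wording with a statement that 128 counts randomised participants.
3. If the sponsor's real target is 114 randomised, keep the abstract, correct the sample-size section and the Overview to match, and restate power as about 87% after 10% loss.

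The first two changes are wording only. They add no participants beyond those the sample-size section already plans and leave the endpoint, the analysis and the calculation untouched. The third also costs only wording, but it would mean acknowledging lower power than the article now claims.

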**Ethics and dissemination:**

Ethics approval has been obtained from East of England–Cambridge South Research Ethics Committee. Results will be disseminated by peer-reviewed publications and conference presentations, and findings will be shared with people living with CF, healthcare providers and relevant stakeholders.

**Trial registration number:**

NCT05562492.

STRENGTHS AND LIMITATIONS OF THIS STUDYThe study adopts an open-label, multicentre, randomised parallel design.The study includes a 26-week follow-up period with equal numbers of study visits between both groups.The study includes young people (≥16 years) and adults with cystic fibrosis-related diabetes, including transplant recipients to support generalisability of the findings.The comparator therapy reflects the current standard of care and includes insulin injections or non-automated insulin pump therapy with continuous glucose monitoring.The study includes both quantitative and qualitative psychosocial evaluation.

## Introduction

 Cystic fibrosis-related diabetes (CFRD) is the most common comorbidity in cystic fibrosis (CF) affecting 15–20% of adolescents and 35–50% of adults.^1 2^ The prevalence of CFRD is increasing, primarily due to improved survival among people with CF .^3^ As individuals with CF live longer, the risk of developing comorbidities such as CFRD also rises. CF transmembrane regulator (CFTR) modulator therapies have significantly transformed CF management by improving lung function and survival of people living with CF. However, there is no clear consensus on their impact on CFRD.^4 5^

The aetiology of CFRD is complex and the mechanisms leading to the development of CFRD are not fully understood. The mechanisms include reduced and delayed insulin secretion, increased insulin resistance and alterations in the regulation of exocrine function. CFRD is associated with increased frequency of pulmonary infections, deterioration in body weight and lung function and a fourfold greater risk of early mortality.^26^,^10^ Among people with CFRD, hyperglycaemia is also associated with an increased risk of death.^11^ Furthermore, with improved survival of people living with CF, long-term microvascular and macrovascular complications associated with diabetes need to be considered.^12^

The recommended management of CFRD is insulin therapy, which is associated with reduced risk of pulmonary infections and improvements in nutritional status and lung function, but adds further to the burden of CF self-management.^13^,^15^ Insulin requirements can be highly variable day to day due to factors such as malabsorption from exocrine pancreatic insufficiency, pulmonary exacerbations, corticosteroid therapy, diet and use of nutritional support, all of which make diabetes management challenging.

There is a need for novel approaches to enable people with CFRD to attain optimal glucose outcomes while minimising any impact on quality of life. Closed-loop systems (also called automated insulin delivery systems) comprise a control algorithm that automatically modulates insulin delivery via an insulin pump in response to continuous glucose monitoring (CGM) measurements. Hybrid closed-loop (HCL) systems are transforming management of type 1 diabetes due to improvements in glycaemic outcomes and reduced burden of diabetes management.^16 17^

The present study will assess whether HCL insulin delivery is safe and effective at improving glycaemic outcomes compared with standard insulin therapy with CGM in people living with CFRD. We will also explore participants’ experiences of using the system and the impact on quality of life in this population.

## Methods and analysis

### Overview

The study adopts an open-label, multicentre, randomised, two-arm, single-period parallel design to assess the effect of HCL insulin delivery with CGM in young people (≥16 years) and adults with CFRD over 26 weeks compared with standard insulin therapy with CGM over 26 weeks (figure 1). Participants include young people aged 16 years and over and adults with CFRD requiring insulin therapy. The study aims for 114 participants completing the study. Recruitment will target up to 128 participants to allow for withdrawals. After a run-in period, eligible participants will be randomly assigned to 26 weeks of study intervention.

### Inclusion criteria

The participant has CFRD requiring insulin therapy for >3 months.The participant is 16 years of age or older.Baseline time in target glucose range <80% during the run-in period.Forced expiratory volume in 1 s (FEV_1_) >30% of predicted mean for age, sex, race and height at the screening visit or within the past 6 months.Participant is willing to wear/carry study devices 24/7 (CGM/insulin pump/smartphone).Participant is willing to follow study-specific instructions.

### Exclusion criteria

Any physical or psychological disease or condition likely to interfere with the normal conduct of the study or interpretation of study results as judged by the investigator.Commencement of CFTR modulator therapy within the previous 1 month.Previous solid organ transplant within the last 12 months or active on transplant waiting list.Use of closed-loop insulin therapy within the past 30 days.Known or suspected allergy to insulin.Severe visual impairment.Severe hearing impairment.Medically documented allergy or unable to tolerate the adhesive of plasters.Serious skin diseases at places of the body corresponding with CGM insertion sites.Participant is pregnant or breastfeeding or planning pregnancy within the next 12 months.

### Study overview

The study includes up to five visits, which can be undertaken in person or remotely with telephone/video link support if preferred, and also includes six telephone/email contacts. Written informed consent will be obtained from all participants before any study-related activities. After a run-in period, participants will be randomised to 26 weeks’ use of HCL insulin delivery or 26 weeks during which they will apply their standard insulin therapy with CGM. Maximum time in the study is 7 months. Table 1 outlines study activities when the participant is randomised to HCL (intervention group). Table 2 outlines study activities when the participant is randomised to standard insulin therapy with CGM (control group).

**Table 1 T1:** Schedule of study visits/contacts when the participant is randomised to closed-loop (intervention group)

	Visit/contact	Description	Start relative to previous/next visit/activity	Duration
Baseline and run-in	Visit 1	Baseline visit: consent, baseline bloods (including HbA1c, C-peptide), height/weight, FEV_1_, urine pregnancy test, questionnaires, masked CGM insertion		1–2 hours
	Visit 2	Review of baseline bloods and CGM data. Randomisation	2–3 weeks after visit 1 (±1 week)	30 min
Postrandomisation training	Visit 3	Study pump, CGM and closed-loop training and initiation, competency assessment	May coincide with visit 2, within 2–4 weeks of visit 1	1–2 hours
CL intervention (26 weeks)	Contact 1	Review use of study devices; study update	Within 48 hours after visit 3	30 min
	Contact 2	Review use of study devices; study update	1 week after visit 3 (±3 days)	30 min
	Contact 3	Review use of study devices; study update; C-peptide measurement	1 month after visit 3 (±2 weeks)	30 min
	Contact 4	Review use of study devices; study update	2 months after visit 3 (±2 weeks)	30 min
	Visit 4	3-month visit FEV_1_, HbA1c, C-peptide, weight, questionnaires, interviews	3 months after visit 3 (±2 weeks)	1 hour
	Contact 5	Review use of study devices; study update; C-peptide measurement	4 months after visit 3 (±2 weeks)	30 min
	Contact 6	Review use of study devices; study update	5 months after visit 3 (±2 weeks)	30 min
	Visit 5	End of closed-loop treatment arm; FEV_1_, HbA1c, C-peptide, weight, questionnaires; resume usual care	6 months after visit 3 (±2 weeks)	1–2 hours

CGM, continuous glucose monitoring; CL, closed-loop; FEV_1_, forced expiratory volume in 1 s.

**Table 2 T2:** Schedule of study visits/contact when the participant is randomised to standard insulin therapy+CGM (control group)

	Visit/contact	Description	Start relative to previous/next visit/activity	Duration
Baseline and run-in	Visit 1	Baseline visit: consent, baseline bloods (including HbA1c, C-peptide), height/weight, FEV_1_, urine pregnancy test, questionnaires, masked CGM insertion		1–2 hours
	Visit 2	Review of baseline bloods and CGM data. Randomisation	2–3 weeks after visit 1 (±1 week)	30 min
Postrandomisation training	Visit 3	CGM training and initiation, competency assessment	May coincide with visit 2, within 2–4 weeks of visit 1	1–2 hours
Standard insulin+CGM (control) (26 weeks)	Contact 1	Review use of study devices; study update	Within 48 hours after visit 3	30 min
	Contact 2	Review use of study devices; study update	1 week after visit 3 (±3 days)	30 min
	Contact 3	Review use of study devices; study update; C-peptide measurement	1 month after visit 3 (±2 weeks)	30 min
	Contact 4	Review use of study devices; study update	2 months after visit 3 (±2 weeks)	30 min
	Visit 4	3-month visit FEV_1_, HbA1c, C-peptide, weight, questionnaires	3 months after visit 3 (±2 weeks)	1 hour
	Contact 5	Review use of study devices; study update; C-peptide measurement	4 months after visit 3 (±2 weeks)	30 min
	Contact 6	Review use of study devices; study update	5 months after visit 3 (±2 weeks)	30 min
	Visit 5	End of standard insulin+CGM treatment arm; FEV_1_, HbA1c, C-peptide, weight, questionnaires; resume usual care	6 months after visit 3 (±2 weeks)	1–2 hours

CGM, continuous glucose monitoring; FEV_1_, forced expiratory volume in 1 s.

### Baseline visit and run-in

At the baseline visit, demographic and medical history data will be collected; questionnaires will be completed; and weight, height and FEV_1_ will be measured. Blood samples for HbA1c and fasted non-hypoglycaemic C-peptide will be collected. A urine pregnancy test will be performed for all females of childbearing age. A masked CGM will be applied to assess baseline glucose levels. They will then proceed to the run-in period (2–3 weeks) where they will use their usual insulin therapy and wear the masked CGM. Participants already using a CGM will continue to use their existing CGM in addition to the masked study CGM during the run-in period. There will be a minimum of 2 weeks’ run-in period for all participants (end of visit 1 to visit 2).

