### Randomisation

At the end of the run-in period (2–3 weeks after visit 1), participants’ CGM data will be reviewed. A minimum of 10 days of data recorded, and less than 80% time in target glucose range, will be needed to proceed with randomisation. Eligible participants will be randomised in a 1:1 ratio to the use of HCL or to standard insulin therapy with CGM for 26 weeks. Randomisation will be done using a centrally administered web-based randomisation sequence with a permuted block design (block sizes 2 and 4) and will be stratified by site, age (≤30 years/>30 years) and baseline time in target glucose range (≤65%/>65%). Participants and investigators will not be masked to the intervention used during each period because of the nature of the interventions.

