### Standard insulin therapy with CGM group (control intervention)

Participants will use the Dexcom G6 CGM. Prior to starting the standard insulin therapy with CGM, participants will be trained on the use of the CGM. Written guidance will also be provided. Competency on the use of study CGM will be assessed. Participants will continue their standard insulin therapy with the study CGM for the next 26 weeks at home.

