### Masked CGM

During the run-in period, participants will wear a masked Dexcom G6 to collect baseline CGM data and to determine eligibility for randomisation.

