#### Primary outcome analysis

The primary analysis will evaluate the between-group difference in the proportion of time spent in the target glucose range of 3.9 and 10.0 mmol/L based on CGM levels during the 26-week intervention period.

The values will be compared using a linear mixed model; the dependent variable is the primary endpoint and the independent variable is treatment allocation, adjusting for baseline time in target glucose range, age and clinical centre. A 95% CI will be reported for the difference between the interventions based on the linear mixed model. Residual values will be examined for an approximate normal distribution. If values are highly skewed, then a transformation or robust statistical method will be used instead. A 5% significance level will be used to declare statistical significance for the primary comparison. A two-sided p value will be reported. The primary analysis will be a single statistical comparison of a single outcome measure.

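### Prior CGM use is plausibly prognostic and known before randomisation, but is missing from the primary model: a modest possible loss of precision, not bias

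*Protocol article*

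**What the plan says.** The protocol article sets the baseline in two places. Under Masked CGM, "participants will wear a masked Dexcom G6 to collect baseline CGM data and to determine eligibility for randomisation". Under Baseline visit and run-in, "Participants already using a CGM will continue to use their existing CGM in addition to the masked study CGM during the run-in period". Prior CGM use is not a bar to entry; the only exclusion for earlier use of diabetes technology is "Use of closed-loop insulin therapy within the past 30 days".

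After randomisation both arms use CGM. In the control arm, "Participants will continue their standard insulin therapy with the study CGM for the next 26 weeks at home", and Table 2 lists CGM training and initiation at visit 3. In the closed-loop arm the sensor is part of the system.

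Randomisation is stratified by site, age (cut at 30 years) and baseline time in range (cut at 65%). The primary linear mixed model compares the arms "adjusting for baseline time in target glucose range, age and clinical centre". Secondary endpoints are to follow the same analysis. Prior CGM use is in neither list.

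**The concern.** For a prior CGM user in the control arm, the study period resembles the run-in as far as monitoring goes. For a CGM starter, baseline was recorded without a CGM display, and the study period then adds one. The same baseline time in range can therefore stand for two different starting positions. Adjusting for the baseline value does not remove the difference, because the value does not carry the monitoring condition with it.

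If starting CGM raises time in range, that gain stays in the residual variance of the primary model. The effect is a wider confidence interval and a treatment estimate that moves with any chance imbalance in CGM starters between the arms. Because the secondary analyses copy the primary model, the omission carries over to time above range, mean glucose and HbA1c.

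The article names its strata and covariates explicitly, so this is a stated choice and not just detail deferred to the analysis plan. If the analysis plan already adds the term, the point falls away.

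**Working it through.** **Inputs from the Sample size calculation section.** Difference 5.0 points, SD 8.1, 90% power, two-sided 5%, 1:1 allocation, 57 per arm (114), 10% loss, 64 per arm (128).

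**Reproducing the plan's figure.** The noncentral t calculation gives power 0.899 at 56 per arm and 0.904 at 57, so 57 per arm (114) is confirmed. Then 57/0.90 = 63.3, rounded up to 64 per arm (128). Power with 64 evaluable per arm would be 0.934.

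**Assumed inputs, not in the documents.** p is the share of prior CGM users, taken as 0.2 to 0.7. g is the gain of CGM starters over prior users at equal baseline, taken as 2 to 5 points and equal in both arms.

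**Formulas.**
- Variance due to prior use: v = p(1−p)g².
- (a) If 8.1 already contains this mixture, the SD after adjustment is √(8.1² − v).
- (b) If the mixture comes on top of 8.1, the SD without adjustment is √(8.1² + v).
- Chance shift in the treatment difference: SD = g√(2p(1−p)/57).

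**Example, p = 0.5, g = 5.** v = 0.25 × 25 = 6.25, which is 6.25/65.61 = 9.5% of the planning variance. (a) gives SD 7.70 and (b) gives SD 8.48. The chance shift has SD 5 × √(0.5/57) = 0.47, so 95% lie within ±0.92.

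**Results at 57 per arm** (N is the total for 90% power):

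| p | g | v/8.1² | Power (a), adjusted | N (a) | Power (b), unadjusted | N (b) | Shift, 95% |
|---|---|---|---|---|---|---|---|
| 0.2 | 2 | 1.0% | 0.907 | 112 | 0.902 | 114 | ±0.29 |
| 0.2 | 5 | 6.1% | 0.921 | 106 | 0.887 | 120 | ±0.73 |
| 0.5 | 3 | 3.4% | 0.914 | 110 | 0.895 | 118 | ±0.55 |
| 0.5 | 5 | 9.5% | 0.930 | 102 | 0.877 | 124 | ±0.92 |
| 0.7 | 5 | 8.0% | 0.926 | 104 | 0.882 | 122 | ±0.84 |

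Under (a) the covariate lifts power from 0.904 to at most 0.930. Under (b) leaving it out lowers power from 0.904 to at worst 0.877. Either way the cost is just under 3 points.

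**The shift and the wider interval are one quantity.** The squared SD of the shift is 2v/57, which is exactly the part of the squared standard error that comes from v. Under (a) at p = 0.5, g = 5, the standard error is 8.1 × √(2/57) = 1.52 unadjusted and 7.70 × √(2/57) = 1.44 adjusted.

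**Type I error.** A simulation with p = 0.5, g = 5, residual SD 8.1 and 4,000 runs gave 0.054 without the covariate and 0.055 with it (Monte Carlo SE about 0.003). Power was 0.868 without and 0.895 with.

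**If the gain occurs only in controls.** With p = 0.5 and g = 5 in the control arm alone, a common main effect averages about 2.5 points and explains 0.25 × 2.5²/65.61 = 2.4% of variance. That is worth about 114 × (1/(1 − 0.024) − 1) ≈ 3 participants, against 114 × (1/(1 − 0.095) − 1) ≈ 12 if the gain is the same in both arms. The treatment effect would then differ by 5 points between prior users and starters.

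**The case against.** The plan adjusts for all its stratification factors, which is standard and valid. Any prognostic factor left out of a model could be raised in the same way; pump versus injections or transplant status would do as well. No figure in the documents shows that starting CGM raises time in range here, or how many participants already use it. In the closed-loop arm an algorithm drives insulin delivery, so the gain from seeing glucose values may be smaller there. If so, a main-effect term recovers little and the question becomes one of effect modification. The type of existing CGM is not specified, so a yes/no term may group unlike users. Finally, changing the primary model of an open-label trial that began recruiting in February 2023 is not free.

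Much of this stands. It limits the size of the point and rules out calling the gain known or predictable. It does not make prior CGM use just another covariate: this factor changes the condition under which the main baseline covariate is measured, and the protocol itself makes the distinction in its run-in rule.

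A reader might infer that the treatment comparison is biased. It is not: randomisation balances prior CGM use in expectation, and simulated type I error is about nominal. A reader might also infer that the trial is underpowered. The documents do not show that. If 8.1 already reflects a mixed population, 114 still gives the stated power. If it does not, the worst case in the assumed range is 0.877. Nor does the masked baseline mean that CGM starters had no glucose information in run-in; the article does not say that other glucose checks stop.

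**Conclusion.** The point holds as a modest, avoidable loss of precision. Baseline time in range is measured under two monitoring conditions that the baseline covariate cannot separate, and a plausibly prognostic factor known before randomisation is left out of both the strata and the model.

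For 20–70% prior users and a gain of 2–5 points in both arms, the cost is up to about 3 points of power. The chance shift of up to about ±0.9 points (95%) belongs to the same variance and is not a second harm; the reported interval already reflects it. Both inputs are assumptions. A smaller gain under closed-loop would shrink the benefit of adjustment and make the treatment difference depend on the mix of prior users and starters enrolled. Recruiting to 128 would offset much of the loss if everyone were evaluable, but that margin is set aside for 10% loss to follow-up.

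**What to change.** Before database lock and before anyone compares outcomes by arm, prespecify CGM use at screening (yes/no) as a fixed effect in the primary model and in the secondary models that follow it. Define what counts as CGM use, since the article does not. Leave the randomisation unchanged: recruitment is under way, and strata of site by age by baseline time in range are already small.

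Report the treatment difference for prior users and starters separately, with confidence intervals and as description only, because the effect may differ between them.

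The cost is 1 degree of freedom, one table and a documented amendment to the analysis model, which may need funder and ethics approval if classed as substantial. No extra visits or participants are needed. Sites must already know each participant's CGM status to apply the run-in rule, but the trial team should confirm that it is captured on the case report form. Added after results by arm are seen, the term would be post hoc and should be labelled as such.
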